### Data Collection

This study will focus on assessing the feasibility of future studies and the acceptability of CBT-f-DDD as an intervention (see Appendix A). To assess feasibility, resources needed to complete the feasibility trial will be recorded including:

- Length of time required for RA to complete assessments and to collect and analyse data, collected from RA time sheets.
- CBT attendance rate, collected from electronic patient records.
- The amount and nature of supervision required, collected from supervision notes.

Recruitment data collected throughout the study will also aid in assessing the feasibility:

- Number of referrals from each source.
- Number of ineligible referrals.
- Reasons for ineligibility.
- Rates and reasons for refusal to be included in the study.
- Rates of attrition.
- Reasons for withdrawing from the study.

We will measure the participants’ acceptability of the intervention and study procedure, and the therapists’ acceptability of the intervention. Attrition rates, and the number of therapy dropouts will also be collected in the measurement of acceptability.

Participants’ acceptability of the intervention as well as the assessment procedures and measures will be collected through an end of intervention questionnaire at T2 and semi-structured qualitative interviews at T3 carried out by RAs. Participants’ acceptability of CBT-f-DDD will be measured through questions regarding which aspects of the treatment they found helpful and unhelpful, their perceived impact of the intervention, and their satisfaction with the intervention and therapists. Additionally, a global measure of change question with a binary response will be asked:

*“Do you feel better? Yes/No”*

Therapists’ acceptability of the intervention will be measured through semi-structured qualitative interviews at T2. This will measure therapist satisfaction with training and supervision, their confidence in delivering the therapy, their views of the intervention’s value, and the perceived impact and feasibility of delivery in standard clinical settings. The therapists’ adherence to the intervention protocol will also be examined in measuring the acceptability of the intervention through:

- Participant’s engagement with CBT-f-DDD and homework tasks using a Likert scale for clinicians to complete,
- A random sample analysis of 10% of audio-recorded therapy sessions evaluated through standardised CBT protocols for adherence to the CBT model using the Cognitive Therapy Scale-Revised (CTS-R) and an adapted CBT-f-DDD checklist (see Appendix B).

Finally, we will make a health economics evaluation of the costs and outcomes of the intervention group versus the standard care group. This will include:

- Baseline data on health service usage using The Client Service Receipt Inventory (32), which collects information of participants’ use of health and social care services, living situation, income, employment and benefits, NHS and private costs.
- Quality of life will be assessed using the EQ5D5L (33) at baseline (T0 assessment) after treatment (T2 assessment) and at 9-month follow up (T3 assessment).

**Clinical Data.** Demographic and clinical data will be collected at baseline interview (T0). The demographic data will include age, gender, ethnicity, education, and employment status. Additionally, clinical demographics will be collected including age of onset of DDD, duration, co-morbid diagnoses, previous treatments for DDD, and type and dosage of current medication. The demographic and clinical data collected on the sample will be used to check the representativeness of the sample.

Secondary clinical outcomes will also be measured to inform future trial design as advised by the CONSORT guidance on feasibility RCTs (34) (see Table 2). These measures will provide preliminary data on the correlation between the baseline and final outcome data, the magnitude and direction of the difference between the two groups and the pooled standard deviation of the primary outcome at baseline. They will also provide data on the feasibility of randomisation, recruitment, retention, and acceptability of the intervention. These data will allow for an evaluation of carrying out a future RCT.

**Table 2.** Clinical Outcomes and Measures

| **Outcome** | **Measure** | **Description** |
| --- | --- | --- |
| **Depersonalisation** | The Cambridge Depersonalisation Scale (CDS) (35) | The CDS is a comprehensive 29 item assessment of depersonalisation over the last 6 months, with each item rated by two Likert scales for frequency and duration of experience. The CDS addresses symptoms consistently reported for individuals experiencing depersonalisation including altered experiences in several sensory modalities and in cognition (35). Scores range from 0-290. |
| **Dissociation** | Dissociative Experiences Scale (DES) (36) | The DES is a self-report, 28-item questionnaire which asks the responder about the percentage of time a range of dissociative experiences happen in their adult life. The questionnaire includes three subscales: ‘Depersonalisation/Derealisation’; Dissociative Amnesia; and Absorption (36). |
| **Depression** | Patient Health Questionnaire 9 (PHQ-9) (37) | The PHQ-9 is the depression module of a larger diagnostic instrument for common mental disorders. The participant is asked to rank symptom frequency of each of the nine DSM-IV criteria for depression on a four-point scale from “0 (Not at all)” to “3 (Nearly every day)”. Scores range from 0-27. |
| **Anxiety** | The Generalised Anxiety Disorder Assessment 7 (GAD-7) (38) | The GAD-7 is a seven-item scale reflecting the criteria for generalised anxiety disorder in the DSM-IV. The participant is asked to rank symptom frequency on a four-point scale from “0 (Not at all)” to “3 (Nearly every day)”. Scores range from 0-21. |
| **Co-Morbidity** | The Clinical Interview Schedule – Revised (CIS-R) (39) | The CIS-R evaluates common mental disorders through assessing the frequency of symptoms in the last month across 14 symptom groups. The symptoms are all ranked from 0-4, with higher ratings indicating greater symptomatology (40).  Scores range from 0-56. |
| **Functioning** | The Work and Social Adjustment Scale (WSAS) (41) | The WSAS is a self-report measure of impaired functioning with five items. The WSAS measures the client’s perceived work and social functional impairments from “0 (Not at all impaired)” to “8 (Severely impaired)”.  Scores range from 0-40. |

**Data Management.** All study data will be kept in electronically and physically secure environments and will be pseudo anonymised via the allocation of a unique alphanumeric identifier. The participants will have individual meetings with a research assistant, allowing participants the privacy and opportunity to discuss any concerns and participants will be able to leave the study at any time, without giving a reason. Additionally, participants will be invited to give feedback on their experiences at all stages of the study.

An independent Participant Advisory Group (PAG), consisting of individuals with lived experience of the condition, will provide feedback on every stage of the study. The PAG will meet at key stages throughout the study to be involved with recruitment, intervention, analysis, and interpretation. Activities of the PAG will include reviewing study materials; input into designing qualitative interview topic guides; and providing a lived experience perspective on recruitment and trial processes.

The Independent Data Monitoring and Ethics Committee (IDMEC) and the Trial Steering Committee (TSC) will comprise of independent investigators operating on behalf of the funders who will meet as they see fit. The IDMEC will have untrammelled access to the unblinded data (if so requested) and will report the results to the TSC. Additionally, the Trial Management Group (TMG) will meet monthly to discuss trial management and proceedings. Trial steering groups will ensure the trial adheres to the study protocol, ensures patient safety, and progresses as communicated to the sponsors and funders.

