### Intervention

CBT for DDD aims to reduce distress associated with DDD symptoms by changing catastrophic attributions through general and personalised psychoeducation; developing a shared formulation of difficulties by linking DDD symptoms to anxiety, mood, and/or past traumas; enhancing coping strategies; and by using cognitive restructuring techniques to modify unhelpful appraisals. CBT-f-DDD theorises that DDD symptoms are reduced by altering the maintenance cycle and associated distress.

The intervention will be delivered in addition to the participant’s TAU over a six-month period. The CBT-f-DDD protocol and training manual developed by ECMH will be provided to therapists during training, and each therapist will adjust these as appropriately determined to the individual needs of the client. The intervention comprises the following components (see Table 1).

**Table 1.** CBT-f-DDD intervention components

| **Engagement and psychoeducation about DDD** |
| --- |
| - Managing expectations and goal setting |
| - General and individualised psychoeducation about DDD |
| **Developing the shared formulation** |
| - Diary keeping and analysis |
| - Identifying external and/or internal triggers |
| - CBT vicious cycle of recent, typical incident |
| **Cognitive strategies: content and process** |
| - Restructuring beliefs about DDD |
| - Recognising thinking biases |
| - Working with cognitive processes to reduce rumination, worry and hypervigilance |
| **Emotional regulation strategies** |
| - Anxiety and mood management strategies |
| - Grounding strategies |
| **Behavioural Interventions** |
| - Psychoeducation about safety seeking behaviours |
| - Behavioural activation |
| - Behavioural experiments - Graded exposure |
| **Working with common co-morbid conditions triggering DDD** |
| - Anxiety disorders, low mood, low self-esteem |
| - Working with negative core beliefs/schemas, procrastination, perfectionism |
| - Substance use |
| **Working with Issues Related to Onset** |
| - Trauma-focused CBT imaginal exposure |
| - Dealing with physical reminders of onset |
| - Chair work where the client uses different chairs to represent different aspects of themselves to foster communication and insights from taking various perspectives |
| **Working with Predisposing Factors** |
| - Working with past trauma or life adversity |
| **Staying Well Plans** |

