### Analyses

We will seek evidence of the feasibility of conducting a larger subsequent RCT by examining the following parameters:

- Power calculation: We will determine the pooled standard deviation for the baseline score of the primary outcome variable, as well as the correlation of the primary outcome at baseline and at follow-up (T3). These data, along with the mean clinically important difference (MCID), will be used in the sample size calculation for a fully powered subsequent study.
- Recruitment: Number of referrals from each source, numbers ineligible, reasons for ineligibility, rates, and reasons for refusal to be included in the study.
- Randomisation: whether groups are balanced and randomisation possible in this environment.
- Withdrawals: Attrition rates and reasons for withdrawing throughout the study, follow-up rates.

Additionally, to fulfil the secondary objectives, descriptive analyses will be performed on the following outcomes: resources needed to complete CBT-f-DDD; health economics evaluation; therapist adherence to CBT-f-DDD; sample characteristics; and acceptability outcomes.

Qualitative data from interviews with therapists and participants will be transcribed and analysed using thematic analysis within NVivo software (supervised by co-applicant [name]). This will be guided by Braun & Clarke’s six stage process (42), and conducted collaboratively to include the perspectives of clinicians and those with lived experience within the research team. Interviews will be recorded using an encrypted device for the audio recording, and data will be stored securely within the NHS. Transcription of this audio recording will be done by a professional external agency which has an over-arching contract with UCL that covers all GDPR issues (as outlined in the collaboration agreement between UCL and C&I). These audio files will be destroyed at the end of the project.

As well as providing an in-depth exploration of treatment experiences and perceived impacts (from both provider and recipient perspectives), analysis will be structured to produce clear summaries of feasibility and acceptability issues as reported by therapists and participants. These analyses will inform therapy and trial process modifications in advance of any subsequent definitive trial.

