### Adverse Events

This is not a high-risk study and we do not anticipate any serious adverse events occurring within the study. However, we have undertaken a Research Risk Assessment and a Data Protection Impact Assessment to identify potential risks to mitigate against these as much as possible in advance. From this a Risk Management Plan was put in place to inform RAs of the appropriate procedure when/if there is a disclosure of suicidal ideation made. Finally, we are aware that within any therapy there is the potential discussion of past difficult events which may cause distress to the participant. All interventions will be carried out by qualified and trained NHS clinicians who will also receive regular, specialised supervision by ECMH.

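### The only global change item is a Yes/No question on feeling better, so it cannot separate participants who felt worse from those who felt unchanged (minor)

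*Protocol*

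**What the plan says.** In the protocol, Data Collection, participants' views of the therapy and of the study assessments are gathered by a questionnaire at T2 and by interviews at T3. For CBT-f-DDD the topics are "questions regarding which aspects of the treatment they found helpful and unhelpful, their perceived impact of the intervention", together with satisfaction. The section then states that "a global measure of change question with a binary response will be asked", and prints it as "Do you feel better? Yes/No". It describes no other global rating of change. It does not say at which visit the item is put, or whether participants in the TAU arm answer it.

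Three other places bear on the point:

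- Adverse Events says that in any therapy "there is the potential discussion of past difficult events which may cause distress to the participant". Table 1, under Intervention, lists "Trauma-focused CBT imaginal exposure" and graded exposure among the components.
- Table 2 lists the clinical scales: CDS (0-290), DES, PHQ-9 (0-27), GAD-7 (0-21), CIS-R (0-56) and WSAS (0-40). Of the last it says: "The WSAS is a self-report measure of impaired functioning with five items". EQ5D5L is taken at T0, T2 and T3.
- Data Collection says that the clinical measures will give preliminary data on "the magnitude and direction of the difference between the two groups".

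**The concern.** The item is presented as a measure of change, but it can register change in one direction only. A participant who ended therapy feeling worse and one who felt no different give the same answer. Acceptability is one of the main questions of this feasibility trial. The protocol itself recognises that the therapy may touch on distressing material. A simple count of participants who say that they feel worse would be a natural part of the acceptability summary, and the item as worded cannot supply it.

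The same limit would apply to any later use of the item as an anchor for worsening on the CDS, because its 'No' group mixes two states.

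**Working it through.** The protocol attaches no figure to this item, so there is nothing to reproduce. The check concerns what the response format can carry. The arm size of 20 comes from Participants and Sample Size. All counts and rates below are assumed for illustration.

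**1. What the answers mean.** There are three possible states: better, unchanged and worse. 'Yes' takes the first and 'No' takes the other two. So No = unchanged + worse, and the number worse can be any whole number from 0 up to the number of 'No' answers.

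**2. Same result, different arms.** Take 20 participants, 10 of whom answer 'Yes':

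| Better | Unchanged | Worse | Item shows | A three-category item shows |
|---|---|---|---|---|
| 10 | 10 | 0 | 10 Yes, 10 No | 0% worse |
| 10 | 8 | 2 | 10 Yes, 10 No | 10% worse |
| 10 | 6 | 4 | 10 Yes, 10 No | 20% worse |
| 10 | 4 | 6 | 10 Yes, 10 No | 30% worse |

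With 12 'Yes' and 8 'No', the number worse lies between 0 and 8, which is 0/20 = 0% to 8/20 = 40%.

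**3. What a 'worse' category would add.** If none of n respondents chose it, the one-sided 95% upper limit on the rate of perceived worsening is 1 - 0.05^(1/n).

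- All 20 answer: 1 - 0.05^(1/20) = 0.139, about 14%.
- 16 answer (20 less the nominal 20% dropout in Sample Size, 20 × 0.8 = 16): 1 - 0.05^(1/16) = 0.171, about 17%.

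The Yes/No item gives no such limit unless everyone answers 'Yes'.

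**4. Would there be anything to count?** The chance that at least one of 20 participants worsens is 1 - (1 - p)^20. For assumed true rates p of 5%, 10%, 15% and 20%, this is 64%, 88%, 96% and 99%. Even at a modest rate, an arm of this size would probably contain a case for the item to record.

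**5. Where else worsening could appear.** A rise on CDS, DES, PHQ-9, GAD-7, CIS-R or WSAS, or a fall on EQ5D5L, can be worked out for each participant. The questions on unhelpful aspects and perceived impact, the T3 interview and the withdrawal reasons are open to negative answers. These routes are real, but each leaves a gap:

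- The use stated for the scales is at group level, and no individual threshold for worsening is given.
- The CDS looks back six months. T2 falls six months after T0, and therapy starts only after T1, about one month after randomisation. The T2 recall period therefore includes some time before therapy.
- Under Procedure, Phase 3, the T3 interview is described for the intervention arm only.
- Withdrawal reasons miss anyone who worsens and stays.

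**The case against.** The strongest reply is that the protocol openly chooses a binary item, contradicts nothing by doing so, and has several better places to find deterioration. Nearly all of this stands, and it limits how far the point can be taken. Four stronger readings are tempting, and the protocol does not support them.

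- **That deterioration cannot be seen in this trial.** It can. Seven scales can move in the adverse direction, and a participant who felt worse has several open questions in which to say so. The limit lies in this item, not in the trial.
- **That the item is confined to the CBT arm.** It sits among questions on CBT-f-DDD, which suggests this. But all participants attend T2, and the T2 questionnaire also covers study procedures that both arms undergo. The text does not settle who answers, and the schedule in Appendix A is not shown. Participants also know their allocation, so a contrast between arms on one subjective item would need cautious reading in any case.
- **That a wrong decision on the definitive trial would follow.** No progression rule, sample size input, primary outcome or safety outcome is tied to this item. Nothing says that it will be read alone, and worsening in a large share of an arm should also show on the scales.
- **That worsening is the harm the protocol predicts.** Adverse Events speaks of possible distress when past events are discussed. That is not the same as being worse overall at the end of treatment, and a three-category item would not measure it directly.

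What the reply does not remove is the plain fact about the wording: an item presented as measuring change merges no change with change for the worse.

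**Conclusion.** The point holds in a limited form and is minor. The protocol's only global change item cannot separate worse from unchanged, so it cannot serve as a patient-rated signal of worsening in the acceptability assessment. Its size is the width of what is left unknown: with k 'No' answers, anywhere from 0 to k participants may have felt worse, for example 0% to 40% of an arm of 20 when k = 8.

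The lack of separation follows from the printed wording alone. The illustrations assume 20 respondents per arm (16 in the alternative) and invented counts. The statement that this is the only global item rests on the protocol text, since the questionnaire itself is not shown.

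**What to change.** Reword the item as: *Compared with when you entered the study, are you: better / about the same / worse?* State that both arms answer it at the existing T2 and T3 assessments. In the acceptability summary, report the 'worse' count by arm beside the numbers whose CDS and PHQ-9 scores rose from T0. This assumes that both scales are taken at T0 and at these visits, which should be checked against the Appendix A schedule. The counts of rises are descriptive: some will reflect ordinary variation in scores, so they should not be presented as a deterioration criterion.

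The cost is a minor form change, with no new visit. No information is lost, because 'better' corresponds to the present 'Yes'. The downside is that Yes/No answers already collected must be reported in a separate row, since their 'No' cannot be divided afterwards.

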## Methods/Design

This project will use a two-arm parallel group (single blinded to assessor) individually randomised design consisting of active CBT treatment versus Treatment As Usual (TAU). Participants will undertake an eligibility assessment (T0) and will be assessed again prior to commencement of treatment (T1). Participants randomised to the treatment condition will receive a minimum of 12 weekly CBT sessions (up to a maximum of 24) during a 6-month intervention window. Once the intervention is complete, all participants will be assessed again (T2, 6 months after the eligibility assessment). The final follow-up assessment will occur for all participants nine months after the eligibility assessment (T3).

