### Aims and Objectives

The aims of the study are to:

1. Investigate the ability to recruit, randomise and retain participants through the study period,
2. Define the parameters to inform the sample size calculation for a future efficacy trial (RCT) (i.e., to obtain the correlation coefficient of scores from the Cambridge Depersonalisation Scale (CDS) at baseline and at follow-up) as well as the pooled standard deviation of the CDS at baseline,
3. To carry out preliminary inferential analyses of the efficacy of the therapy to check if a signal has been detected in the treatment arm versus the control arm (so as to inform a subsequent larger RCT if appropriate). These analyses may include estimating the magnitude and direction of the treatment effect as well as obtaining an estimate of the uncertainty in the estimate.
4. To perform a within-trial economic evaluation to compare the costs and outcomes of the intervention group versus the standard care group,
5. Disseminate specialist CBT-f-DDD skills to generic NHS clinicians,
6. Determine whether CBT-f-DDD can be conducted within typical NHS settings with generic CBT therapists given a brief training in DDD.

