### Participants

The study will aim to recruit 40 participants, 20 participants in each arm. All participants will be aged between 16-75, living in London, and have symptoms of Depersonalisation and/or Derealisation currently meeting DSM-V (1) criteria for DDD. This will be assessed by the research assistant (RA) in their initial (T0) screening interview by asking the participant the following two questions, which make up part of the diagnostic criteria in the DSM-V (1) :

“Over the last two weeks, how often have you had:

1. Experiences of unreality, detachment, or being an outside observer with respect to one's thoughts, feelings, sensations, body, or actions (e.g., perceptual alterations, distorted sense of time, unreal or absent self, emotional and/or physical numbing). [Depersonalisation]

0 =not at all; 1=several days; 2=more than half the days; 3=nearly every day”

1. Experiences of unreality or detachment with respect to surroundings (e.g., individuals or objects are experienced as unreal, dreamlike, foggy, lifeless, or visually distorted). [Derealisation]

0=not at all; 1=several days; 2=more than half the days; 3=nearly every day.”

The total score will be calculated as follows:

1. Total score = (a + b).
   1. Scores <3 = mild-moderate DDD.
   2. Scores >=3 = moderate-severe DDD.

Other DSM-V criteria will be assessed including intact reality testing, that the symptoms result in significant distress and/or functional impairment, and that the DDD symptoms cannot be better explained by another condition. Participants will be excluded if they have any of the following co-morbid diagnoses: any psychosis spectrum disorder, substance dependence, intellectual disability, Post Traumatic Stress Disorder (PTSD), or cognitive impairment due to head injury or organic disorder. Comorbidity with anxiety and/or depressive disorders will not be an exclusion criterion.

Additionally, participants will be excluded from the study if they have previously received CBT specifically for the treatment of DDD; have a score below clinical severity (i.e. total score < 3) on the diagnostic questions; cannot provide informed consent; do not have sufficient proficiency in English to engage in CBT; require special communication needs arrangements; are not registered with a GP practice or are involved in any other mental or physical research studies (including drug trials).

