**Training of Therapists.** Training of therapists will take place in half-day workshops. All therapists involved will be qualified and have experience with CBT. We will collect data about whether therapists included in the study are accredited with the British Association of Behavioural and Cognitive Psychotherapists (BABCP) and their past qualifications and years of experience with CBT. The training workshops will aim to help therapists understand DDD and demonstrate the adaptation of existing CBT skills to work with DDD using clinical case examples. All therapists will receive a hard copy of the training manual with additional materials and reading. As this is a feasibility study, we will also be examining whether a half-day training would be sufficient to supply these skills and knowledge.

There is an agreement with the relevant C&I and BEH Heads of Services that therapists across the trusts will attend the training in order to be able to take on one or more cases of DDD clients. We envisage having a relatively large number of therapists with a small trial caseload to reduce the burden on services and to maximise the number of therapists who will benefit from training and specialist supervision.

**Phase 2: Treatment Phase***.* Prior to commencing therapy and one month after randomisation, the participants in both arms will be assessed again (T1). Those in the intervention arm will receive a minimum of 12 (maximum of 24) 1-hour-long CBT-f-DDD sessions. The location of these sessions will depend on participant and/or therapist preference and can be conducted face-to-face or via videoconferencing. Meta-analyses comparing the efficacy of psychological therapies conducted face-to-face versus through videoconferencing has shown similar symptomatic improvement and client satisfaction scores across conditions (28, 29). Additionally, a recent RCT examining online versus in-person CBT for anxiety conditions did not find a significant difference in outcome measures between treatment conditions (30). It is not expected that this study will find any differences between the two conditions but will collect the modality used for monitoring purposes. The CI [ECMH] will provide fortnightly group specialist supervision to therapists delivering the intervention. For those in the TAU arm, there will be a record kept of the type and frequency of their appointments with clinical services and the treatments offered.

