## Discussion

This paper presents the protocol for a feasibility study investigating a cognitive behavioural therapy intervention for individuals with DDD. This research came about after two clinical audits from a national specialist NHS service indicated that CBT adapted for DDD might be of benefit. However, these were small scale, from a specialist service and participants had not been randomised, so the next step in both research and treatment provision in this clinical population was to identify whether a future RCT is feasible and whether the intervention, CBT-f-DDD, is acceptable to both clinicians and clients. The findings of the feasibility study will aid in establishing the key parameters for a future RCT trial (if appropriate). Additionally, this feasibility paper will also help in dissemination of information about CBT-f-DDD for up to 20 clinicians, hopefully increasing awareness and improving accuracy in diagnoses of DDD for both NHS trusts involved.

Protocol version: V6.6 September 2023

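### The 10% fidelity sample is drawn by session with no minimum per therapist, so some briefly trained therapists may go unrated; stratifying by therapist would prevent this, normally within the same 10%

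*Protocol*

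**What the plan says.** The fidelity sample is defined in the Data Collection section of the protocol: "A random sample analysis of 10% of audio-recorded therapy sessions evaluated through standardised CBT protocols for adherence". The sampling unit is the recorded session. The text mentions no stratification by therapist, client or stage of therapy, and no minimum per therapist.

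The questions these ratings bear on concern therapists. Aim 6 is to "Determine whether CBT-f-DDD can be conducted within typical NHS settings with generic CBT therapists given a brief training in DDD". The Procedure section, under the training of therapists, adds: "we will also be examining whether a half-day training would be sufficient to supply these skills and knowledge".

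Staffing is described only loosely. The same section says "We envisage having a relatively large number of therapists with a small trial caseload", and that therapists will attend training so as to be able to "take on one or more cases of DDD clients". The Discussion mentions "dissemination of information about CBT-f-DDD for up to 20 clinicians". On volume, the Participants section states "The study will aim to recruit 40 participants, 20 participants in each arm", and Methods/Design says that those allocated to CBT "will receive a minimum of 12 weekly CBT sessions (up to a maximum of 24) during a 6-month intervention window".

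**The concern.** The unit sampled and the unit asked about differ. A draw over the pooled sessions settles how many sessions are rated, but leaves to chance which therapists they come from. Spreading a small treatment arm over many therapists makes it more likely that a 10% draw misses some of them. A therapist's chance of being rated also rises with the number of sessions delivered, so short courses are covered least.

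Other evidence on Aim 6 is planned: therapist interviews, supervision notes, attendance and clinician-rated engagement. None of it is a direct rating of what happens in the session. If some therapists have no rated session, the trial can describe average fidelity over sessions but cannot show how delivery varied over all the therapists it trained and used.

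**Working it through.** The protocol gives no figure for therapist coverage, so there is nothing to reproduce. The check asks how many therapists an unstratified 10% draw would be expected to miss.

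**Inputs from the protocol.** CBT arm: 20 participants (Participants). Sessions per participant: 12 to 24 (Methods/Design). Share rated: 10% (Data Collection). Clinicians: up to 20 (Discussion), each with one or more cases (Procedure).

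**Assumptions.** All sessions are recorded, course lengths are equal unless stated, and the draw is unstratified. The number of treating therapists is varied because the protocol does not fix it.

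**Formula.** Let N be all recorded sessions, n = 0.10 × N the number rated, m the sessions of one therapist, and T the number of therapists. Then P(therapist has no rated session) = C(N − m, n) / C(N, n), and the expected number unrated is T × P.

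**One client each, T = 20.**
- 12 sessions: N = 240, n = 24; C(228, 24)/C(240, 24) = 0.274; × 20 = 5.5 unrated.
- 18 sessions: N = 360, n = 36; P = 0.143; × 20 = 2.9 unrated.
- 24 sessions: N = 480, n = 48; C(456, 48)/C(480, 48) = 0.075; × 20 = 1.5 unrated.

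As a rough check, 0.9 to the power m gives 0.282, 0.150 and 0.080, close to the exact values. In 5,000 simulated draws, at least one therapist was unrated in about 100%, 98% and 83% of draws. The 5th to 95th percentiles of the number unrated were 3–8, 1–5 and 0–3. With course lengths uniform on 12 to 24, the mean was 3.1 (1–5).

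**Expected number of unrated therapists, by caseload:**

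| Therapists and caseload | 12 sessions | 18 sessions | 24 sessions |
| --- | --- | --- | --- |
| 20, one client each | 5.5 | 2.9 | 1.5 |
| 15 (10 with one client, 5 with two) | 3.1 | 1.5 | 0.8 |
| 10, two clients each | 0.70 | 0.18 | 0.05 |
| 5, four clients each | about 0 | about 0 | about 0 |

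**Shorter courses.** The first uncontrolled study in the Background had a median of 11 sessions. At 11 sessions and one client each, 6.1 of 20 would be unrated; at 8 sessions, 8.4.

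**Does stratifying fit in the same 10%?** One session from each of 20 therapists needs 20 ratings. The 10% quota is 24, 36 or 48 at 12, 18 or 24 sessions. The quota covers every therapist when 0.10 × N ≥ T, that is, when recorded sessions average at least 10 per therapist. At 8 each, N = 160 and the quota is 16, so 20 − 16 = 4 extra ratings would be needed.

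**Why the overall average needs weights.** Suppose one session is drawn per therapist and the other n − T are drawn at random from the rest. A session of a therapist with m sessions is then selected with probability 1/m + (1 − 1/m)(n − T)/(N − T). With 12 sessions each this is 1/12 + (11/12)(4/220) = 0.100, so no weighting is needed. With ten therapists at 12 sessions and ten at 24 (N = 360, n = 36), it is 1/12 + (11/12)(16/340) = 0.126 for the shorter courses and 1/24 + (23/24)(16/340) = 0.087 for the longer ones. An unweighted mean would over-represent short courses.

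**The case against.** The strongest reply is that the protocol says only that the sample is random. It neither prescribes simple random sampling nor rules out stratification, and a fidelity procedure could still add it. This is correct, so the point is not an error or a contradiction. It is that the rule as written does not secure coverage, and one sentence would.

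A reader might infer that many therapists will go unrated. The protocol does not support that. The figure of 20 clinicians is an upper bound, given in connection with dissemination, and therapists may take more than one case. Caseload drives the result: over 12 to 24 sessions, two clients per therapist bring the expected number below one. Still, the protocol itself envisages many therapists with small caseloads, so one client each is the upper end of its plan and not an invented case.

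A reader might also infer that the fidelity result is biased or that Aim 6 fails. Neither follows. A random sample of sessions gives an unbiased average over recorded sessions, and weighting by course length is proper to that target. The Analyses section promises only a descriptive account of therapist adherence, no CTS-R threshold is set, and other evidence also bears on Aim 6.

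A further tempting step is to say that therapists whose clients stop early matter most for judging the training. The protocol does not link early stopping to therapist skill, so this is conjecture. Only the arithmetic stands: fewer sessions mean a lower chance of being rated.

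Finally, one rated session per therapist is thin. With 24 ratings over 20 therapists, at least 16 would have exactly one. That objection stands, and it limits what the fix can deliver.

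**Conclusion.** The point holds as an inexpensive design improvement. The fidelity sample is defined by session with no floor per therapist, while the question it serves is about therapists. Under the planned pattern of small caseloads, taken as 20 therapists with one client each, 12 to 24 sessions and complete recording, about 1.5 to 5.5 of 20 would be expected to have no rated session (7.5% to 27% each). With two clients per therapist over the same range the expected number is below one, and with four it is about nil. The size therefore rests on a caseload that the protocol does not fix.

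What is at risk is coverage of every treating therapist and a complete picture of the spread between them. The average over sessions is not at risk.

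**What to change.** In Data Collection, state that the 10% sample will be stratified by therapist: at least one randomly chosen recorded session from each therapist who treats a trial participant, and the remainder of the 10% drawn at random from the other recordings. Describe CTS-R and checklist scores by therapist as well as overall, and weight the overall session average by the inverse of each session's selection probability.

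The cost is a sentence or two in the protocol and slightly more analysis. The number of ratings is unchanged if recorded sessions average at least 10 per therapist; below that a few more are needed (four in the example of 8 sessions for each of 20 therapists). The report should say that one session per therapist gives coverage and a view of the spread, which also contains session-to-session variation, and is not a firm judgement on any single therapist.
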